**2.1 Primary Objectives**

- Dose-Limiting Toxicity (DLT)

To evaluate the safety, tolerability, and determine the recommended dosage of allo-DNT cell therapy for AML subjects after allo-HSCT. Time Frame: Up to 28 days.

- Maximum Tolerated Dose (MTD)

MTD was the highest dose for DLT in ≤1/6 subjects. Time Frame: Up to 28 days.

- Incidence of abnormalities: Incidence of abnormalities in AE/SAE/laboratory tests/electrocardiograms/vital signs. Time Frame: Up to 28 days.

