**SYNOPSIS**

**Title：Allo-DNT Cells for the Prevention of Relapse in AML Patients After Allo-HSCT**

**Objective**

To evaluate the safety and tolerability of healthy donor-derived double negative T cells (DNTs) infusion in acute myeloid leukemia (AML) patients after allogeneic hematopoietic stem cell transplantation (allo-HSCT).

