**2.2 Secondary Objectives**

- Pharmacokinetics (PK) indicator (Cmax)

The peak concentration of allo-DNT cells amplified in the peripheral blood (Cmax, detected by Flow Cytometry). Time Frame: Up to 2 years.

- Pharmacokinetics (PK) indicator (AUC)

Allo-DNT cells blood concentrations will be measured at different time points to evaluate the area under the curve (AUC). (AUC, detected by Flow Cytometry). Time Frame: Up to 2 years.

- Pharmacokinetics (PK) indicator (Tmax)

Allo-DNT cells blood concentrations will be measured at different time points to evaluate the peak time (Tmax) in peripheral blood. Tmax is defined as the time to reach the highest concentration (Tmax, detected by Flow Cytometry). Time Frame: Up to 2 years.

- Pharmacokinetics (PK) indicator (T1/2)

Allo-DNT cells blood concentrations will be measured at different time points to evaluate the elimination half-life in hours (T1/2). T1/2 is defined as the time point when the concentration of allo-DNT reaches half of maximum in a patient’s peripheral blood (T1/2, detected by Flow Cytometry). Time Frame: Up to 2 years.

- Recurrence rate at 6 months

Record the proportion of patients with recurrence in the study. Time Frame: Up to 6 months.

- Relapse-free survival (RFS)

Relapse-free survival is the time from study enrollment until documented disease relapse, or death from any cause. Time Frame: Up to 2 years.

- GvHD-free and relapse-free survival (GRFS)

GRFS is the time from study enrollment until documented disease relapse, or death, or GvHD occur from any cause. Time Frame: Up to 2 years.

- 2-year overall survival

From the date of entry into the clinical study until death from any cause. Time Frame: Up to 2 years.

1. **TRIAL DESIGN**

The trial is divided into two parts: Part A is a dose escalation trial with two dose groups (1.0×10^8 cells/kg, 1.5×10^8 cells/kg at day 0, day 28 and day 56), with 6-12 patients planned to be enrolled. Part B is a dose-expansion randomized controlled trial in which 40-60 patients will receive RC1012 infusions at recommended phase II dose (RP2D) levels. Patients at the end of the infusion will continue to be followed up for a total of 2 year.

1. **ELIGIBILITY**
   1. **Subject Eligibility**
      1. **Inclusion Criteria**

- Voluntarily sign an ICF and expect to complete the study procedures for follow-up examinations and treatment.
- Aged 18 to 70 years (including cut-offs), regardless of gender.

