- Subject has been involved in other clinical studies within 3 months prior to screening.
- Subject in the judgement of the investigator and/or clinical criteria, is contraindicated to any study procedure or have other medical conditions that may place them at unacceptable risk.
  - 1. **Criteria for Removal from the Study**
- The occurrence of intolerable toxicity during infusion prevents the subject from continuing RC1012 injection treatment.
- The subject may choose to withdraw from the clinical trial at any time by informing the researcher.
- Hematologic relapse of the patient’s disease occurs, and the researcher evaluates that cell infusion is not appropriate.
- The subject experiences death, withdrawal of informed consent, or is lost to follow-up during the trial.
- Other situations where the researcher deems cell infusion inappropriate.
  1. **Donor** **Eligibility**
     1. **Inclusion Criteria**
- Age ≥ 18 years old.
- Healthy person who meets the requirements of blood donation in central blood station.
- There is no disease that can be transmitted through blood within 30 days before blood collection (HIV, HBsAg, HBcAb, HCV antibody, syphilis serological test, CMV IgM, and EBV IgM all negative).
- The cytotoxicity of DNTs to at least three myeloid leukemia cell lines (OCI-AML3, MV 4-11, K562, U937, etc.) (target to efficiency ratio 4:1) ≥ 20%, or to patient primary AML cells ≥ 10%.
  - 1. **Exclusion Criteria**
- There are chronic diseases that need to be treated, such as hypertension, diabetes, heart disease, thyroid disease and liver and kidney insufficiency.
- Bone marrow diseases.
- Pregnancy.
- Systemic glucocorticoids must be used before peripheral blood taking.
- Paroxysmal psychosis.
- Poison and drug addiction.

1. **TREATMENT PLAN**
   1. **Ex vivo expansion of DNTs and Infusion**

According to the established expansion method (Patent number: PCT/CA2006/001870), DNTs will be expanded *ex vivo* under GMP conditions. DNTs will be assessed for purity and microorganism and endotoxin contamination before infusion. After enrollment, patients will receive once a month with total three times infusion of DNTs product at escalating doses of 1×10^8^, or 1.5×10^8^/kg. Subjects' vital signs will be assessed, and pulse oximetry will be done during the infusion.

- 1. **Supportive Treatment**

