All medication treatments administered to the subject from the onset of AML until the end of this study (including RFS and OS follow-up periods) should be documented. This includes prescription drugs, over-the-counter medications, traditional Chinese medicine, Chinese patent medicines, and herbal preparations. Additionally, the subject’s medical history for other diseases from the time of signing the informed consent until the end of the treatment period (28 days after the last cell infusion) must also be recorded. Except for the prohibited medications specified in the study protocol, all other medications may continue to be used. From the initiation of RC1012 injection infusion until hematologic relapse or a change in the treatment regimen, unless otherwise specified in the protocol, the subject is not allowed to use the following treatments:

- Anti-tumor therapies (including traditional Chinese medicine, Chinese patent medicines, and herbal preparations with anti-tumor properties);
- Corticosteroids, as they may interfere with the activity of the product, should be avoided as a preventive measure. However, they may be used if necessary, such as in cases of CRS (Cytokine Release Syndrome);
- Any other medications that could affect the investigator's ability to assess efficacy or subject safety.
  1. **Assessment**
- Clinical Assessment: Clinical assessment including vital signs (e.g., blood pressure, pulse and temperature) and complications should be assessed every day during the cycle of therapy.
- Hematological examination: should be assessed 2-3 times per week. Blood routine should be monitored daily when ANC ＜ 1.0×10^9^/L and (or) platelet count ＜ 20×10^9^/L.
- Urine routine will be tested before each cycle of therapy and be retested after treatment according to the condition.
- Stool Routine: Stool routine will be tested before each cycle of therapy. Stool routine should be retested in time when patient have diarrhea, and bacterial and fungal culture should be carried out to exclude infectious diarrhea.
- Biochemistry: Biochemistry will be assessed before infusion and at least weekly for each cycle of therapy.

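### The primary safety incidence endpoint has a 28-day window with no start point; counted from the first infusion, it closes on the day of the second of three infusions

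*Protocol*

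**What the plan says.** The Synopsis gives the trial's objective as "To evaluate the safety and tolerability of healthy donor-derived double negative T cells (DNTs) infusion" in AML patients after transplant. Section 2.1 of the Protocol then lists three primary items, all with the same time frame: DLT, MTD ("MTD was the highest dose for DLT in ≤1/6 subjects. Time Frame: Up to 28 days") and "Incidence of abnormalities in AE/SAE/laboratory tests/electrocardiograms/vital signs. Time Frame: Up to 28 days". None of the three states a start point.

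Section 3 sets the Part A infusions "at day 0, day 28 and day 56", "with 6-12 patients planned to be enrolled". Section 5.1 agrees on the number: "patients will receive once a month with total three times infusion of DNTs product".

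Other sections bear on the window without setting it:

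- Section 5.2 asks for the history of other diseases to be recorded "until the end of the treatment period (28 days after the last cell infusion").
- Section 5.3 says that vital signs and complications "should be assessed every day during the cycle of therapy" and asks for biochemistry at least weekly in each cycle. ECGs are done only when clinically indicated.
- Section 6.3 has staff monitoring adverse events for the whole study.
- Section 7.1 counts an adverse event from the first study treatment onward.

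**The concern.** The regimen under test is three infusions, and its safety and tolerability are the stated objective. If the primary incidence rate stops 28 days after the first infusion, it says almost nothing about the second and third. A reader could nevertheless take it for the rate over the whole course.

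The missing start point adds a second problem. Two analysts working from the same sentence could use Day 0-28 or Day 0-84 and report different primary safety figures.

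The concern is limited to Part A, where the infusion days are stated, and to the incidence endpoint. A DLT window confined to the first infusion is an accepted choice and is not the objection.

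**Working it through.** **Inputs.** Window length: 28 days (Section 2.1). Infusion days: 0, 28 and 56 (Section 3). End of treatment period: 28 days after the last infusion (Section 5.2). Part A size: 6 to 12 patients (Section 3). All three infusions are assumed to be given to every patient.

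**Where the window ends, by start point.**

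| Start of the 28 days | Window | Infusions with 28-day follow-up inside |
| --- | --- | --- |
| First infusion | Day 0 to 0 + 28 = Day 28 | 1 of 3 |
| Last infusion only | Day 56 to 56 + 28 = Day 84 | 1 of 3 |
| Each infusion in turn | Day 0 to Day 84 | 3 of 3 |

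Any single 28-day window therefore holds the 28-day follow-up of at most one infusion. Only a per-infusion reading covers all three. If monthly is taken as about 30 days (an assumption), a window from the first infusion closes about 2 days before the second. A start at enrolment before Day 0 closes it earlier still.

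**Which reading the text supports.** Two things favour the first infusion: the incidence item carries the same time frame as the DLT and MTD items directly above it, and Section 7.1 starts adverse events at the first study treatment. In the other direction, where the protocol does tie a 28-day interval to an infusion, it uses the last or third one (Sections 5.2 and 5.3). It says so explicitly in those places and does not do so in Section 2.1.

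**Exposure inside a Day 0-28 window.**

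- Treatment days: 28 / 84 = 0.333.
- Infusions given: 6 × 3 = 18 to 12 × 3 = 36.
- Infusions with their 28-day follow-up inside: 6 × 1 = 6 to 12 × 1 = 12 (one third).
- Infusions with it outside: 18 − 6 = 12 to 36 − 12 = 24 (two thirds).
- Patient-days in total: 6 × 84 = 504 to 12 × 84 = 1008.
- Patient-days inside: 6 × 28 = 168 to 12 × 28 = 336.
- Patient-days outside: 504 − 168 = 336 to 1008 − 336 = 672.

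These figures measure exposure and not event rates. The protocol gives no event risk from which an understatement could be calculated.

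**The case against.** The strongest reply is that the harm depends on a start point the protocol does not state. The DLT and MTD items have no start point either, so borrowing theirs is weak support. Section 7.1 says when an event begins to qualify as an adverse event but not when counting stops, and it does not address the laboratory, ECG or vital-sign components. The exact counting rule might also be left to an SAP. This stands as far as it goes: the first-infusion reading is the natural one, but it is not the only one. It does not remove the problem, because the protocol fixes a length of 28 days and no single window of that length covers the course. An SAP that used Day 0-84 would have to reinterpret or depart from the stated time frame.

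A second reply is that tabulating adverse events over the DLT window suits a dose-finding part, and that course-long safety is covered elsewhere. Section 6.3 tracks all AEs and SAEs and analyses changes from baseline with no 28-day limit, and RFS, GRFS and OS run to 2 years. Section 6.1 even names the 6-month relapse rate as the main outcome and lists safety separately. It is true that the data will exist and that later events can be reported. But Section 2.1 calls this rate primary, and later events still fall outside it on the natural reading.

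A third reply is that the size given is exposure only, that the 84-day period is borrowed from a sentence about recording other diseases, and that no test or threshold uses the rate. All of this is correct. It limits the weight of the point but does not change what the reported figure would describe.

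**Conclusion.** The concern holds. The primary incidence endpoint has a stated length and no start point. On the natural reading it covers 28 of 84 treatment days and the 28-day follow-up of one infusion in three, so it does not describe the regimen named in the objective. In Part A, the follow-up of 12-24 of 18-36 infusions falls outside the primary rate.

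This rests on counting from the first infusion, on all three infusions being given, and on taking Section 5.2's end of treatment as the natural end of the course. The effect on the reported rate is unknown. It may be zero if events cluster after the first infusion or if most patients already have some abnormality by Day 28. Dose decisions and data capture are unaffected. The issue should be fixed because the repair is cheap and the rate is a primary one. Confidence is medium because another reading of the window is possible.

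**What to change.** In Section 2.1, change the time frame of the incidence endpoint to *from first infusion to 28 days after the last infusion (about Day 84)*. For DLT and MTD, keep 28 days and add *from first infusion*; that addition is clarification only.

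The cost is the wording of three time frames. No new data collection is needed, because the Section 5.3 assessments already run through each cycle and adverse events are monitored throughout. The ECG component would use whatever ECGs exist, as it does now. The downsides are slightly more tabulation and possibly a less favourable figure, since a longer window also counts more background post-transplant events. The timing of DLT, MTD and RP2D decisions does not change.

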**2.2 Secondary Objectives**

- Pharmacokinetics (PK) indicator (Cmax)

The peak concentration of allo-DNT cells amplified in the peripheral blood (Cmax, detected by Flow Cytometry). Time Frame: Up to 2 years.

- Pharmacokinetics (PK) indicator (AUC)

Allo-DNT cells blood concentrations will be measured at different time points to evaluate the area under the curve (AUC). (AUC, detected by Flow Cytometry). Time Frame: Up to 2 years.

- Pharmacokinetics (PK) indicator (Tmax)

Allo-DNT cells blood concentrations will be measured at different time points to evaluate the peak time (Tmax) in peripheral blood. Tmax is defined as the time to reach the highest concentration (Tmax, detected by Flow Cytometry). Time Frame: Up to 2 years.

- Pharmacokinetics (PK) indicator (T1/2)

Allo-DNT cells blood concentrations will be measured at different time points to evaluate the elimination half-life in hours (T1/2). T1/2 is defined as the time point when the concentration of allo-DNT reaches half of maximum in a patient’s peripheral blood (T1/2, detected by Flow Cytometry). Time Frame: Up to 2 years.

- Recurrence rate at 6 months

Record the proportion of patients with recurrence in the study. Time Frame: Up to 6 months.

- Relapse-free survival (RFS)

Relapse-free survival is the time from study enrollment until documented disease relapse, or death from any cause. Time Frame: Up to 2 years.

- GvHD-free and relapse-free survival (GRFS)

GRFS is the time from study enrollment until documented disease relapse, or death, or GvHD occur from any cause. Time Frame: Up to 2 years.

- 2-year overall survival

From the date of entry into the clinical study until death from any cause. Time Frame: Up to 2 years.

1. **TRIAL DESIGN**

The trial is divided into two parts: Part A is a dose escalation trial with two dose groups (1.0×10^8 cells/kg, 1.5×10^8 cells/kg at day 0, day 28 and day 56), with 6-12 patients planned to be enrolled. Part B is a dose-expansion randomized controlled trial in which 40-60 patients will receive RC1012 infusions at recommended phase II dose (RP2D) levels. Patients at the end of the infusion will continue to be followed up for a total of 2 year.

1. **ELIGIBILITY**
   1. **Subject Eligibility**
      1. **Inclusion Criteria**

- Voluntarily sign an ICF and expect to complete the study procedures for follow-up examinations and treatment.
- Aged 18 to 70 years (including cut-offs), regardless of gender.
- Subject must be diagnosed with AML according to World Health Organization (WHO) criteria (2016).
- The subject has received an allo-HSCT within 60-100 days, the percentage of malignant primitive cells in the bone marrow is < 5% after HSCT and STR-PCR shows complete donor chimerism.
- The subject has one of the following high-risk factors for relapse after allo-HSCT: (1) Failure to achieve remission after two courses of induction chemotherapy. (2) Prior history of Myelodysplastic Syndromes (MDS) or Myeloproliferative Neoplasm (MPN). (3) High leukocytes (≥100×10^9/L) combined with Central Nervous System Leukemia (CNSL); (4) Positive Minimal Residual Disease (MRD) before HSCT; (5) Non-remission or disease progression prior to HSCT; (6) Subject with cytogenetic high-risk factors (except that who can be treated with targeted drugs).
- The subject has recovered from the toxicity of the prior treatment, i.e., CTCAE toxicity grade <2 (unless the abnormality is tumor-related).
- ECOG score 0 to 1.
- With appropriate organ function:
- • Glutathione aminotransferase (AST) ≤ 3 times the upper limit of normal (ULN);
- • Glutamic aminotransferase (ALT) ≤ 3 times ULN;
- • Total bilirubin ≤ 1.5 times ULN, unless the patient has documented Gilbert syndrome. Patients with Gilbert-Meulengracht syndrome with total bilirubin ≤ 3.0 times ULN and direct bilirubin ≤ 1.5 times ULN may be included;
- • Serum creatinine ≤ 1.5 times ULN or a creatinine clearance ≥ 60 ml/min;
- • Hemoglobin ≥ 80 g/L or hemoglobin maintained at that level following transfusion;
- • International Normalized Ratio (INR) ≤ 1.5 times ULN and Activated Partial Thromboplastin Time (APTT) ≤ 1.5 times ULN;
- • Absolute neutrophil count (ANC) ≥ 1.5 x 10^9/L.
- • A platelet count ≥ 50 x 10^9/L or a platelet count maintained at that level following a platelet transfusion;
- • Left ventricular ejection fraction (LVEF) ≥ 45%.
- Female patients with childbearing potential should have a negative pregnancy test during the screening period. Any male and female patients of childbearing potential must agree to use an effective contraception method for at least six months from the time that they sign the informed consent form until the end of the cell infusion. Female patients without childbearing potential (meeting at least 1 of the following criteria) is described below.
- • Have undergone a hysterectomy or bilateral oophorectomy;
- • Medically recognized as ovarian failure;
- • Medically recognized as post-menopausal (at least 12 consecutive months of menopause without pathological or physiological cause).
  - 1. **Exclusion Criteria**
- Patients with active grade II to IV acute GvHD or extensive chronic GvHD.
- Subject is confirmed to have morphological relapse of leukemia or positive MRD after allo-HSCT.
- Subject with extramedullary infiltration of leukemia.
- Suffer from other malignancies within 5 years prior to screening, except adequately treated carcinoma in situ of the cervix, basal cell or squamous epithelial cell skin cancer, post-radical thyroid cancer, and post-radical ductal carcinoma in situ.
- Has severe respiratory disease (previous or combined history of severe interstitial lung disease, severe chronic obstructive pulmonary disease, severe pulmonary insufficiency, symptomatic bronchospasm).
- A previous history of a definite neurological or psychiatric disorder, including epilepsy or dementia.
- Evidence of active central nervous system invasion or cranial neuropathy.
- Patients with positive hepatitis B surface antigen (HBsAg) or hepatitis B core antibody (HBcAb) and peripheral blood hepatitis B virus (HBV) DNA titration assay not within the normal reference range, positive hepatitis C virus (HCV) antibody and peripheral blood HCV RNA ,positive for human immunodeficiency virus (HIV), or positive for cytomegalovirus (CMV) DNA, or positive syphilis test.
- Subject who is allergic to the excipients of RC1012 injection or other drugs recommended in the study protocol (e.g., tolimumab, etc.).
- Serious cardiac disease, including but not limited to severe arrhythmia, unstable angina, massive heart attack, New York Heart Association class III or IV cardiac insufficiency, refractory hypertension.
- Persons who have previously received an organ transplant or are preparing to receive an organ transplant (except for HSCT).
- Subject who has received other maintenance therapy drugs after HSCT or who wish to receive other maintenance therapy.
- Subject with the presence of acute GvHD of degree III to IV or extensive chronic GvHD.
- Active neurological autoimmune or inflammatory diseases (e.g. Guillain-Barre Syndrome (GBS), Amyotrophic lateral sclerosis (ALS)).
- Clinically significant active cerebrovascular disease (e.g. cerebral oedema, Posterior Reversible Encephalopathy Syndrome (PRES)).
- Subject with a life expectancy of less than 3 months.
- Subject has been involved in other clinical studies within 3 months prior to screening.
- Subject in the judgement of the investigator and/or clinical criteria, is contraindicated to any study procedure or have other medical conditions that may place them at unacceptable risk.
  - 1. **Criteria for Removal from the Study**
- The occurrence of intolerable toxicity during infusion prevents the subject from continuing RC1012 injection treatment.
- The subject may choose to withdraw from the clinical trial at any time by informing the researcher.
- Hematologic relapse of the patient’s disease occurs, and the researcher evaluates that cell infusion is not appropriate.
- The subject experiences death, withdrawal of informed consent, or is lost to follow-up during the trial.
- Other situations where the researcher deems cell infusion inappropriate.
  1. **Donor** **Eligibility**
     1. **Inclusion Criteria**
- Age ≥ 18 years old.
- Healthy person who meets the requirements of blood donation in central blood station.
- There is no disease that can be transmitted through blood within 30 days before blood collection (HIV, HBsAg, HBcAb, HCV antibody, syphilis serological test, CMV IgM, and EBV IgM all negative).
- The cytotoxicity of DNTs to at least three myeloid leukemia cell lines (OCI-AML3, MV 4-11, K562, U937, etc.) (target to efficiency ratio 4:1) ≥ 20%, or to patient primary AML cells ≥ 10%.
  - 1. **Exclusion Criteria**
- There are chronic diseases that need to be treated, such as hypertension, diabetes, heart disease, thyroid disease and liver and kidney insufficiency.
- Bone marrow diseases.
- Pregnancy.
- Systemic glucocorticoids must be used before peripheral blood taking.
- Paroxysmal psychosis.
- Poison and drug addiction.

1. **TREATMENT PLAN**
   1. **Ex vivo expansion of DNTs and Infusion**

According to the established expansion method (Patent number: PCT/CA2006/001870), DNTs will be expanded *ex vivo* under GMP conditions. DNTs will be assessed for purity and microorganism and endotoxin contamination before infusion. After enrollment, patients will receive once a month with total three times infusion of DNTs product at escalating doses of 1×10^8^, or 1.5×10^8^/kg. Subjects' vital signs will be assessed, and pulse oximetry will be done during the infusion.

- 1. **Supportive Treatment**

All medication treatments administered to the subject from the onset of AML until the end of this study (including RFS and OS follow-up periods) should be documented. This includes prescription drugs, over-the-counter medications, traditional Chinese medicine, Chinese patent medicines, and herbal preparations. Additionally, the subject’s medical history for other diseases from the time of signing the informed consent until the end of the treatment period (28 days after the last cell infusion) must also be recorded. Except for the prohibited medications specified in the study protocol, all other medications may continue to be used. From the initiation of RC1012 injection infusion until hematologic relapse or a change in the treatment regimen, unless otherwise specified in the protocol, the subject is not allowed to use the following treatments:

- Anti-tumor therapies (including traditional Chinese medicine, Chinese patent medicines, and herbal preparations with anti-tumor properties);
- Corticosteroids, as they may interfere with the activity of the product, should be avoided as a preventive measure. However, they may be used if necessary, such as in cases of CRS (Cytokine Release Syndrome);
- Any other medications that could affect the investigator's ability to assess efficacy or subject safety.
  1. **Assessment**
- Clinical Assessment: Clinical assessment including vital signs (e.g., blood pressure, pulse and temperature) and complications should be assessed every day during the cycle of therapy.
- Hematological examination: should be assessed 2-3 times per week. Blood routine should be monitored daily when ANC ＜ 1.0×10^9^/L and (or) platelet count ＜ 20×10^9^/L.
- Urine routine will be tested before each cycle of therapy and be retested after treatment according to the condition.
- Stool Routine: Stool routine will be tested before each cycle of therapy. Stool routine should be retested in time when patient have diarrhea, and bacterial and fungal culture should be carried out to exclude infectious diarrhea.
- Biochemistry: Biochemistry will be assessed before infusion and at least weekly for each cycle of therapy.
- Serum Cytokine Levels: Cytokines will be measured before infusion of DNTs, then 6, 24, 48 hours, 5d, 7d after each DNT infusion, and 14d, 21d, 28d after the 3^rd^ infusion. Serum cytokines included interleukin-6 (IL-6), interferon (IFN)-γ, IL-8, IL-10, tumor necrosis factor (TNF)-α, macrophage inflammatory protein (MIP)-1α, MIP-1β, monocyte chemoattractant protein (MCP-1), and soluble receptors IL-1Rα and IL-2Rα.
- Assessment of DNTs in vivo: Peripheral blood aspirates will be analyzed by FACS to assess and quantify the percentages of DNTs before infusion, then 6, 24, 48 hours, 5d, 7d after each DNT infusion, and 14d, 21d, 28d after the 3^rd^ infusion.
- Electrocardiogram (ECG): ECGs should be performed when clinically indicated.
- Bone Marrow Analysis: Bone marrow aspirates will be obtained before the first cycle of DNTs therapy and 28 days after the 3^rd^ infusion. After achieving CR, analyze once a month.
  1. **Follow-up**

Patients will be followed-up for survival data for 2 year from the date of start of treatment. Blood routine, biochemistry and bone marrow studies will be obtained monthly as clinically indicated to assess disease. Analyses will include morphologic examination of the aspirate, FACS, and cytogenetics when indicated.

1. **TREATMENT RESPONSE/OUTCOME ASSESSMENT**
   1. **Main Outcome Measurement**

Cumulative relapse rate at 6 months post-treatment.

- 1. **Secondary Outcome Measurement**

Relapse-free survival (RFS), GvHD-free relapse-free survival (GRFS), and 2-year overall survival (OS) post-cell infusion.

- 1. **Safety Measurement**
- Safety assessment indicators include vital signs, clinical laboratory tests (complete blood count, blood biochemistry, coagulation function, urinalysis), 12-lead electrocardiogram (ECG), and physical examination. Throughout the study, research center staff will monitor adverse events.
- Adverse Events (AEs): The occurrence of all AEs and serious adverse events (SAEs) will be tracked. Changes from baseline in laboratory tests (including complete blood count, urinalysis, blood biochemistry, coagulation function), 12-lead ECG, physical examination, and vital signs (temperature, respiration, blood pressure, and pulse) will be analyzed.
- Dose-limiting toxicities (DLTs) and maximum tolerated dose (MTD) (Phase I only): Cytokine release syndrome (CRS) will be graded according to the ASTCT 2019 criteria, while other AEs will be graded based on the NCI-CTCAE version 5.0. The frequency and severity of DLTs will be assessed to determine the MTD for the subjects.
  1. **Response Assessment**
- Complete Remission (CR): Bone marrow blasts < 5%; absence of circulating blasts and blasts with Auer rods; absence of extramedullary disease; ANC≥1.0×10^9^/L; platelet count ≥100×10^9^/L;
- CR without MRD (CR MRD^-^): If studied pretreatment, CR with negativity for a genetic marker by RT-qPCR, or CR with negativity by MFC;
- CR with incomplete recovery (CRi): All CR criteria except for residual neutropenia (< 1.0 ×10^9^/L or thrombocytopenia (< 100 ×10^9^/L);
- Morphologic leukemia-free state (MLFS): Bone marrow blasts < 5%; absence of blasts with Auer rods; absence of extramedullary disease; no hematologic recovery required;
- Partial Remission (PR): All hematologic criteria of CR; decrease of bone marrow blast percentage to 5% to 25%; and decrease of pretreatment bone marrow blast percentage by at least 50%;
- Treatment failure: Failure to achieve CR or PR
  1. **Relapse**
- Hematologic relapse: after achieving CR MRD^-^, CR, or CRi in AML patients, the reappearance of leukemic cells in peripheral blood or ≥5% blasts in bone marrow (excluding other causes such as bone marrow regeneration after consolidation chemotherapy), or leukemic cell infiltration at extramedullary sites.
- Molecular relapse: after achieving CR MRD^-^, the reappearance of MRD positivity detected by standard methods [e.g., RT-qPCR or multiparametric flow cytometry (MFC) with a sensitivity of at least 10^-3^].
  1. **Survival**
- Overall Survival (OS): From the date of entry into the clinical study until death from any cause.
- Relapse-Free Survival (RFS):  the time from study enrollment until documented disease relapse, or death from any cause.

1. **ADVERSE EVENT REPORTING**
   1. **Definitions**
      1. **Adverse Event**

An AE is any undesirable sign, symptom or medical condition or experience that develops or worsens in severity after starting the first study treatment in the protocol, even if the event is not considered to be related to the study.

- - 1. **Serious Adverse Event**

A SAE is any adverse event, occurring at any dose and regardless of causality that:

- Fatal
- Life-threatening
- Requires or prolongs hospital stay
- Results in persistent or significant disability or affecting the ability to work
- [Congenital](javascript:;) [malformation](javascript:;)
- Carcinogenic
- Important medical event means an event that will not immediately be life-threatening or result in death or hospitalization, but may endanger the subject or require measures to prevent the occurrence of any of the above. For example, angioneurotic edema that do not require tracheal intubation but require corticosteroid therapy, or intensive treatment of bronchospasm.
  1. **Attribution**

Attribution is the relationship between an adverse event or serious adverse event and the study treatment. Attribution will be assigned as follows:

- Definite: The AE is clearly related to the study treatment.
- Probable: The AE is likely related to the study treatment.
- Possible: The AE may be related to the study treatment.
- Unlikely: The AE is doubtfully related to the study treatment.
- Unrelated: The AE is clearly NOT related to the study treatment.
  1. **Procedures for AE and SAE Recording and Reporting**
- The adverse event report form should be filled in truthfully during the study. Record the time, severity, duration, measures and outcome of AE. AE should be recorded in the Adverse event Reporting Form of CRF.
- Any SAE must be reported to the [major](javascript:;) [investigator](javascript:;), the ETHICS committee and [research](javascript:;) [center](javascript:;)  as soon as possible but no later than 24 hours. The investigator must fill out the SAE form, recording the time, severity, duration, measures and outcome of SAE.
  1. **Follow-up of AE**

AE should be followed until remission or stable symptoms, and follow-up of SAE may need to continue until the end of the study.

- 1. **Gestation**

If patient get pregnant during the trial, stop the drug immediately and fill in the pregnancy report form of clinical trial. To ensure the safety of each patient, researcher should report to the sponsor within 24 hours of knowing the pregnancy. Patient should be followed up until the outcome is clear, including abortion or automatic termination of pregnancy, details of delivery, presence of any birth defects, or congenital [malformation](javascript:;), or maternal and neonatal complications.

1. **QUALITY MANAGEMENT**
   1. **Investigators**

- Investigators qualification: Investigators participating in clinical trials must be checked qualification and have the professional background and ability to conduct clinical trials.
- Training of researchers: Receiving training programs arranged by clinical trial institution for each project is a prerequisite to qualify investigators. After the approval of the medical ethics committee, the Principle Investigator (PI) will organize training.
  1. **Clinical Monitors**

Representatives of the Sponsor will conduct a site initiation visit and periodically audit, at mutually convenient times during and after the study, all CRFs and corresponding source documents for each subject. The monitors will verify that investigational products are properly stored and accounted for, verify that subjects’ consent for study participation has been properly obtained and documented, confirm that research subjects entered into the study meet inclusion and exclusion criteria.

- 1. **Standardized Operation**

The sponsor complies with the Drug Clinical Trial Quality Management Standard (2003 edition) and the Drug Registration Regulations. DNTs will be expanded ex vivo under GMP condition. Ensure the high quality for them.

- 1. **Laboratory Examination**

The research center will conduct laboratory tests in accordance with standard operating procedures (SOP).

1. **DATA HANDLING AND RECORD KEEPING**
   1. **Data Collection**

The Case Report Form (CRF) will comprise a set of forms capturing details of eligibility, baseline characteristics, treatment and outcome details etc. All entries will be entered into an electronic data capture system (EDC). PI is responsible for assuring that the data entered into eCRF is complete, accurate, and that entry and updates are performed in a timely manner.

- 1. **Data Retention**
- It is the investigator’s responsibility to retain study original documents. Original data include original records, informed consent signed by subjects, laboratory data, imaging data, ECG, medication records, etc.
- The researchers center should keep the basic data of subjects for a longer time according to the regulations (at least 5 years).

1. **SAMPLE SIZE**

Part A is a dose escalation trial with two dose groups, 6-12 patients planned to be enrolled. Part B is a dose-expansion randomized controlled trial in which 40-60 patients will receive RC1012 infusions at RP2D dose levels.

1. **REFERENCE**

